### Process evaluation

Drawing on Linnan and Steckler’s framework [29], a process evaluation will be conducted throughout the intervention period. The process evaluation will be used to explain results and potential impacts on participants by assessing implementation per-protocol across study sites. This work will address four components of process evaluation: fidelity, sustainability, reach, and context [29]. Fidelity to the protocol will be achieved through standardized training and measurement of skill acquisition among Elders, teachers, and students throughout the intervention. Standardization of delivery will be supported by routine monitoring and review of the manualized intervention, observation of the classroom, and brief discussions with participants to assess facilitators and barriers to implementation. A protocol and manual outlining the process and content of the HIV stigma curriculum will be developed to support fidelity to intervention protocols [29].

Students, teachers, and Elder participants will be invited to participate in summative interviews to generate additional data for the process evaluation (5-10 students will be purposively selected from each of the three crossover groups). We will also randomly select ten CAC members to interview at the end of the study.

### Outcomes

Outcomes will include self-reported stigma-related measures and clinical measures. The primary outcomes are enacted, anticipated, and internalized stigma as measured using the *Adolescents Living with HIV—Stigma Scale* [30]. Secondary outcomes will include courtesy and perceived stigma measured using *Stewart et al.’s 10-item subscale* [31] and the *Brief Stigma by Association Scale* [32]. Secondary clinical outcomes will include HIV testing frequency among sexually active participants; and linkage to care, time to initiation of antiretroviral therapy (ART), ART adherence, and viral suppression, among participants living with HIV. Study outcomes will be assessed by independent research team members at baseline, following each crossover period (i.e., every 8 weeks), and 5-months after completion of the final intervention block.

### Power calculation

Using the power and detectable-difference calculations for stepped-wedge cluster-randomized trials (91) (Stata 14.2), we calculated 98% power to detect a 20% reduction (i.e., an absolute risk difference of 12%) in the proportion of young people reporting a stigma endpoint (i.e., endorsing sufficient elements in the primary stigma measure) given a baseline proportion of 60% experiencing HIV-related stigma, a 5% two-tailed type I error rate, and an intra-cluster correlation coefficient (ICC) of 0.01. There is a lack of published ICC estimates in this setting. Prior work in sub-Saharan Africa and rural Uganda found that 50% of participants experienced stigma in some form [33]. Given our team’s prior experience working among young people in areas recovering from conflict, we have assumed a higher baseline proportion of 60% to have experienced HIV-related stigma. We targeted a total cluster size of 12, with four schools (two primary and two secondary) grouped to crossover from control to intervention at three specified crossover points. We estimate that there will be 150 students enrolled per school across eligible grade levels. Assuming a 50% participation rate after attrition, we estimate that the evaluation will reach 75 students per school for a total sample of *n*=900 who will complete the surveys at the end of the final data collection period﻿ [34].

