### Setting and participants

This study will take place in Omoro District, Northern Uganda, where the HIV prevalence among the 15–24 age group at 7.2% is 20% greater than the national prevalence of 6.0% [23]. Omoro District has a slightly higher pregnancy rate among young people of 28% among 10–18 year-olds compared to the national rate of 25%. HIV prevalence among young pregnant mothers who were tested at their first antenatal visit was 8.9% in the district compared to 7.6% for pregnant mothers nationally [23].

In Omoro District, there are seven secondary and 65 primary government-funded schools that serve six sub-counties (Koro, Lalogi, Odek, Bobi, Ongako, Lakwana, and Omoro). Each grade level enrolls approximately 50 students per school, with approximately 12,000 students enrolled across these grades. In this study, we will approach students ≥10 years of age in six grade levels for recruitment. Primary grades 5–7 include approximately *n*=150 students per school; secondary grades 1–3 include *n*=150 students per school. Therefore, we estimate *n*=1800 as the total number of eligible students attending 12 schools across eligible grade levels.

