### Data collection and management

#### Survey design and measurements

A survey questionnaire will assess primary and secondary outcomes, along with selected covariates. The questionnaire will be developed in English and translated into Luo. The questionnaire will be refined with input from the CAC and pretested with 6–10 students to evaluate ease of comprehension, suitability of questions, and completion issues. Internal consistency of relevance scales (e.g., attitudes, stigma) will be assessed using Cronbach’s alpha.

The questionnaire will take up to 60 min to complete and will include questions about socio-demographics, reproductive and sexual health behavior, HIV testing, and HIV care. Stigma outcomes will be measured using three validated scales:Enacted, anticipated, and internalized stigma among HIV-positive students will be measured using the *Adolescents Living with HIV—Stigma Scale* [30].Courtesy stigma will be measured using the *Brief Stigma by Association Scale in HIV-affected students* [31].Perceived stigma will be measured using *Stewart’s 10-item subscale on felt-normative stigma towards PLHIV* in their community [32].

As intervention benefits may attenuate over time [35], we will examine sustainability of attitudinal change and stigma-associated change five months after the intervention has ended. Sexual risk, HIV testing frequency, and HIV status will be assessed by self-report.

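### The stated 98% power counts every surveyed student, but the survey section measures the primary stigma scale only among HIV-positive students, for whom power is far lower on the plan's own figures

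*Protocol article*

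**What the plan says.** Power calculation (protocol article): "we calculated 98% power to detect a 20% reduction (i.e., an absolute risk difference of 12" points. The endpoint is defined "in the proportion of young people reporting a stigma endpoint (i.e., endorsing sufficient elements in the primary stigma measure"). The assumed starting level is worded as "given a baseline proportion of 60% experiencing HIV-related stigma"; the error rate and correlation are set at "a 5% two-tailed type I error rate, and an intra-cluster correlation coefficient (ICC) of 0.01". On numbers, "we estimate that the evaluation will reach 75 students per school", which over 12 schools is 900. The section does not reduce this to a subgroup.

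Outcomes: "The primary outcomes are enacted, anticipated, and internalized stigma as measured using the" Adolescents Living with HIV—Stigma Scale. No population is attached to that sentence.

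Survey design and measurements: "Enacted, anticipated, and internalized stigma among HIV-positive students will be measured using the" same scale.

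Objectives: change in all five stigma types is to be assessed in HIV-positive and HIV-affected young people together.

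Intervention components: eligibility rests on age, residence, school and grade. HIV status plays no part.

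Setting and participants gives the only prevalence for young people in general: "where the HIV prevalence among the 15–24 age group at 7.2" per cent.

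**The concern.** The power statement and the survey section describe different denominators for the same endpoint. The first counts every student expected to complete the survey; the second counts only those living with HIV, who are a small minority on the prevalence the article quotes. If the survey section is right, the power figure does not apply to any of the three primary outcomes. Readers, funders and ethics committees would believe that a 12-point fall is almost certain to be detected, and a null result could then be misread as evidence that the intervention does not work.

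**Working it through.** **Inputs from the article.** 12 schools; three sequences of four; four 8-week periods (Study design); 60% falling to 48%; two-sided 5%; ICC 0.01; 75 students per school; prevalence 7.2%.

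**Formula.** Hussey-Hughes variance for a stepped wedge with I schools, T periods, g the sampling variance of a school-period mean and t the between-school variance:

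Var = I·g·(g + T·t) / [(I·U − W)·g + (U² + I·T·U − T·W − I·V)·t]

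With I = 12 and T = 4, the design gives U = 24, W = 224, V = 56. Then I·U − W = 288 − 224 = 64, and the second bracket is 576 + 1152 − 896 − 672 = 160. So

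Var = 12·g·(g + 4t) / (64g + 160t).

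Total variance at the mean proportion: 0.54 × 0.46 = 0.2484. So t = 0.01 × 0.2484 = 0.002484, and g = 0.99 × 0.2484 / m = 0.2459 / m for m students per school-period. Power = Φ(0.12/SE − 1.96). Detectable difference at 80% power = (1.96 + 0.84) × SE = 2.80 × SE.

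**Step 1: the plan's figure.** m = 75: g = 0.003279; Var = 12 × 0.003279 × 0.013215 / (0.20985 + 0.39744) = 0.000856; SE = 0.0293; power = Φ(4.10 − 1.96) = 98.4%. Other variance conventions give 98.3% to 98.7%. Splitting the 75 over the four periods gives about 60%, and 150 per school gives 99.99%. The stated 98% thus matches all 75 students contributing in every period.

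**Step 2: HIV-positive students only.** 900 × 0.072 = 64.8; 64.8 / 12 = 5.4 per school. g = 0.04554; Var = 12 × 0.04554 × 0.05548 / (2.9146 + 0.3974) = 0.00915; SE = 0.0957; power = Φ(1.254 − 1.96) = 24%.

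**Step 3: following the same students.** The analysis section plans assessments within participants within schools. For an assumed correlation ρ between repeated answers of one student within a school, replace t by t + ρ·g and g by (1 − ρ)·g. At ρ = 0.5: t = 0.02525, g = 0.02277, Var = 0.00615, SE = 0.0784.

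| Students per school | Assumed ρ | SE | Power, 60% vs 48% | Detectable at 80% power |
|---|---|---|---|---|
| 75 | none | 0.0293 | 98.4% | 8.2 points |
| 5.4 | none | 0.0957 | 24.0% | 26.8 points |
| 5.4 | 0.5 | 0.0784 | 33.4% | 22.0 points |
| 5.4 | 0.7 | 0.0624 | 48.6% | 17.5 points |
| 5.4 | 0.8 | 0.0514 | 64.6% | 14.4 points |

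The choice of variance convention moves these powers by about a point. The detectable differences hold the variance at 0.2484 and are approximate.

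**Step 4: range of prevalence (assumed), 900 students, cross-sectional.** At 2% (1.5 per school) power is 10%; at 10% (7.5 per school) it is 31%.

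**Step 5: what would be needed.** 80% power on the cross-sectional calculation takes about 32 HIV-positive students per school, and 32/75 is about 43% of those surveyed.

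**The case against.** **The denominator is not settled.** The restriction to HIV-positive students is stated for this scale only in the survey section. The Outcomes section attaches no such limit to the primary outcomes, although it does limit the treatment outcomes to participants living with HIV. The Objectives speak of HIV-positive and HIV-affected young people, and the formative interviews may lead to changes in the survey instruments. This stands: the firm finding is that the sections disagree, and the low power is conditional on the survey section. It does not rescue the power statement, because no section explains why every surveyed student should count. If all were meant to answer, the survey section needs correcting instead.

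**A reader might infer that the true power is simply 24%.** The documents do not support a single figure. It treats each period's students as new people, whereas the planned model follows the same students, and it borrows a prevalence for ages 15–24. With repeated measures the figure rises to about 33% to 65%.

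**Fuller participation would help.** If all 1800 eligible students took part, 1800 × 0.072 / 12 = 10.8 per school. Cross-sectional power is then about 41%. By the step 3 substitution it is about 58%, 78% and 91% at ρ of 0.5, 0.7 and 0.8. So 80% can be passed, but only by dropping the plan's own 50% participation and assuming a high correlation.

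**Other tempting inferences.** One might say that 5.4 per school is optimistic because enrolment starts at age 10; the article gives no prevalence for younger students, so the direction is not established. One might say that only students who disclose their status can be counted; the section on administrative health data also obtains HIV status from linked clinic records. One might call the 98% an arithmetic slip; it is computed correctly for the denominator used.

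**Conclusion.** The point holds in conditional form. The article is inconsistent about who contributes the primary endpoint, and its 98% belongs to an endpoint answered by all 75 students per school. On the survey section's reading, with 900 students and an assumed 7.2% prevalence, about 65 students contribute. Power for the 12-point difference is then about 24% cross-sectionally, or 33% to 65% with assumed within-student correlations of 0.5 to 0.8, so it stays below 80% throughout that range. The size rests on three things the documents do not fix: the share of HIV-positive students among those enrolled, the within-student correlation, and the reading of the survey section. This is not a complaint about detail left to an analysis plan: the article states a power figure that its own description of the measurement contradicts.

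**What to change.** 1. Reconcile the Objectives, Outcomes, Power calculation and survey sections on who answers the primary scale.
2. If it is HIV-positive students only, restate power and detectable difference for the primary outcomes on their expected number, under the planned repeated-measures model, over a stated range of prevalence and within-student correlation.
3. Say that the 98% holds only for an endpoint that all 75 students per school answer, with the assumed 60% baseline.

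Replacing the primary outcome with perceived stigma is not part of this fix. It would be a redesign, the survey section does not say that every student answers that scale, and the 60% baseline is not tied to it.

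Cost: a text amendment and a less favourable stated power. No extra data are needed.

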#### Analysis of survey data

Descriptive statistics will be used to assess balance between clusters and to describe schools relative to the required sample size at each timepoint, socio-demographic characteristics, and primary/secondary outcomes. Main analyses will use linear mixed effect models (LMEM) or generalized linear mixed effect models (GLMEM) to assess the intervention effect. LMEM will be used for continuous outcomes that approach normality and GLMEM will be used for binary and other types of outcomes. Normality will be assessed using model residuals and outliers by Cook’s distance, leverage, and residuals. Time in weeks from the beginning of the trial, time in weeks centered at the beginning of the intervention, time in weeks from the beginning of school semesters, and blocks will be specified as fixed effects. The multilevel structure will be defined by assessments within participants as level one, participants as level two, and schools as level three. Schools and participants within schools will be specified as random effects. Main analyses will follow an intention-to-treat approach, with clusters analyzed as per the original treatment assignment. Sensitivity analyses will be performed to assess bias arising from attrition. A significance level of 0.05 will be used in all statistical tests. Analyses will be conducted in SAS v9.4.

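### The primary stigma endpoint is given a form only in the power calculation, as a yes/no cut with no threshold, and it is not tied to the named scale outcome or to one analysis model

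*Protocol article*

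**What the plan says.** Four places in the protocol article bear on the form of the primary outcome.

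- **Outcomes:** "The primary outcomes are enacted, anticipated, and internalized stigma as measured using the" chosen scale, which is the Adolescents Living with HIV—Stigma Scale. It does not say whether the outcome is a score, a change or a proportion.
- **Power calculation:** the planned effect is a fall "in the proportion of young people reporting a stigma endpoint (i.e., endorsing sufficient elements in the primary stigma measure"). Its size and the claimed power are "98% power to detect a 20% reduction (i.e., an absolute risk difference of 12" percentage points). The starting level is 60%, the test is two-sided at 5%, and the ICC is taken as 0.01. The section assumes 75 students per school in 12 schools, 900 in all. What counts as sufficient is not defined.
- **Survey design and measurements:** "Enacted, anticipated, and internalized stigma among HIV-positive students will be measured using the" same scale, so the primary scale belongs to HIV-positive students.
- **Analysis of survey data:** "LMEM will be used for continuous outcomes that approach normality and GLMEM will be used for binary and other types of outcomes". Neither model is assigned to the primary outcomes.

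Objective 1 asks for the magnitude of change in the stigma measures.

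**The concern.** The trial is sized on a yes/no version of a scale built from several elements. A student whose score falls a good deal but stays on the same side of the cut counts as unchanged. A student who moves one element across it counts as a full response. If the analysis follows that endpoint, precision is lost for no stated gain, and the loss matters most where few students answer the scale. If the analysis uses the score, the published power belongs to a different endpoint. In both cases the Outcomes, Power calculation and Analysis of survey data sections do not describe one and the same primary analysis. An undefined threshold also leaves the cut open to choice after the data are seen.

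**Working it through.** **Inputs from the protocol.** 12 schools, 4 crossing at each of 3 steps, 4 periods; 60% against 48%; ICC 0.01; two-sided 5%; 75 students per school.

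**Inputs assumed.** A near-normal score. The number of HIV-positive students is not stated. The only local youth prevalence is 7.2% at ages 15-24 (Setting and participants). Applied to 75 students it gives 0.072 × 75 = 5.4 per school, about 65 of 900. The sample is aged 10 and over, so I show 1.5 (2% of 75) to 10 per school.

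**Step 1: formula.** The Hussey-Hughes variance of the treatment effect is

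Var = I·s·(s + T·t) / [(I·U − W)·s + (U² + I·T·U − T·W − I·V)·t],

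where s = (1 − ICC)·v/m, t = ICC·v, v is the outcome variance and m the students per school per period. Here I = 12, T = 4, U = 24, W = 0 + 16 + 64 + 144 = 224 and V = 4 × (9 + 4 + 1) = 56. So I·U − W = 64, and the second bracket is 576 + 1152 − 896 − 672 = 160.

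**Step 2: the plan's own figure.** Binary variance v = (0.24 + 0.2496)/2 = 0.2448. With m = 75, s = 0.003231 and t = 0.002448.

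Var = 12 × 0.003231 × (0.003231 + 0.009792) / (64 × 0.003231 + 160 × 0.002448) = 0.000844.

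SE = 0.0290, z = 0.12/0.0290 = 4.13, power = Φ(4.13 − 1.96) = 98.5%. The stated 98% is reproduced as a binary calculation with 75 students per school contributing in every period.

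**Step 3: information kept by the cut.** On a normal score, 60% against 48% is a shift of 0.2533 + 0.0502 = 0.3035 SD. The binary contrast is worth 0.12/√0.2448 = 0.2425 SD. The ratio squared is (0.2425/0.3035)² = 0.639. The local formula φ(z)²/[p(1 − p)] gives 0.622 at p = 0.60, 0.634 at 0.54 and 0.636 at 0.48. The cut therefore keeps about 62-64%.

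**Step 4: power, cut against score.** Same formula; for the score, v = 1 and the effect is 0.3035.

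| Students per school | Cut | Score | Difference |
|---|---|---|---|
| 75 | 98.5% | 99.9% | just under 1.5 points |
| 10 | 39% | 56% | about 17 |
| 5.4 | 24% | 35% | about 11 |
| 3.6 | 18% | 26% | about 8 |
| 1.5 | 10% | 13% | about 3 |

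At 5.4 per school, the binary SE is 0.0950 and z = 1.26; the score SE is 0.192 and z = 1.58.

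**Step 5: sensitivity at 5.4 per school.** With ICC 0.05 the figures are 22% and 32%; with ICC 0.10, 22% and 31%. The formula treats periods as separate samples, whereas the planned model has repeated assessments within students. With an assumed within-student correlation of 0.5 the figures are 34% and 49%; with 0.7, about 50% and 68%. The level of power moves, but the direction of the difference does not.

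**The case against.** The strongest reply is that a binary power calculation discards nothing by itself. Information is lost only if the analysis is binary, and no section says that it will be. The Outcomes section names the scale without a cut, Objective 1 speaks of magnitude of change, Cronbach's alpha is planned for the scales, and the linear mixed model is available. Planning on a proportion also has a visible reason: the baseline is anchored to earlier work reporting that 50% experienced stigma, and no scale SD is cited. If the score is then analysed, the binary calculation is conservative at 75 per school. Scoring rules are also commonly left to a full protocol or SAP, which is not shown here.

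Most of this stands. A reader might infer that the trial has committed to a dichotomised primary analysis and so throws away a third of its information; the analysis section does not support that. A reader might also blame the cut for power near 24%. That figure comes from replacing 75 students by an assumed 5.4, which is the population mismatch and not the dichotomy.

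The reply does not remove the gap. The article does more than leave the form to a later document: it states one, and rests its 98% on it without a threshold or a link to the outcome or the model.

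**Conclusion.** The point holds in a conditional form. Either the primary analysis follows the stated binary endpoint and keeps about 62-64% of the information, or it uses the score and the 98% is not its power. The cost of the first branch is just under 1.5 points at 75 students per school. It is roughly 3 to 17 points if only HIV-positive students contribute, under the assumed 1.5 to 10 per school.

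These sizes rest on a near-normal score; the item count, response format and distribution are not given, and a skewed or floor-heavy score would change them. The HIV-positive count is an inference from a prevalence for ages 15-24.

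Analysing the score does not rescue the trial's power: at 5.4 per school, power stays near 35% in the simple model. The mismatch between a calculation on all 900 students and a scale for HIV-positive students is separate and larger (about 98% down to about 24%), and should be judged on its own.

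**What to change.** In Outcomes, Power calculation and Analysis of survey data, state that each primary outcome is the full subscale score, analysed with the linear mixed model, with an ordinal or robust analysis of the same score if it is skewed. The generalized mixed model already allowed can hold the ordinal version. Keep the proportion above the cut as a secondary result and state its threshold. Restate power for the score in the students who answer the scale, using an SD from the pretest or baseline, or the 0.30 SD shift implied by 60% against 48%.

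The cost is wording in three sections and one recalculation; no further data are needed, because the scale is already in the questionnaire. The downside is that the main result is in scale points rather than a percentage, which the secondary proportion covers. Trial status places study recruitment ahead of the protocol date, so the change could be made before outcome data exist.

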**Fig. 1 Fig1:**
[figure not shown]
SPIRIT flow diagram

The 32-week stepped-wedge cluster-randomized trial will be implemented in three blocks of four schools, each stratified by school type (primary, secondary), such that each block will consist of two schools of each type. The clusters are assembled into three blocks that will crossover from control to intervention condition, with crossover order selected at random. Including the control period, each school will participate across four 8-week periods with crossover from control to intervention condition occurring after each period [20, 21]. Clusters will receive the intervention over 24 weeks, 16 weeks, or 8 weeks depending on their block allocation (Fig. 2).

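### The 98% power counts all 75 students per school, although the primary scale is for HIV-positive students only; its missing within-student correlation is a smaller, mostly conservative mismatch

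*Protocol article*

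**What the plan says.** All references are to the protocol article.

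- **Power calculation.** It states: "we calculated 98% power to detect a 20% reduction (i.e., an absolute risk difference of 12" percentage points, "given a baseline proportion of 60% experiencing HIV-related stigma". The endpoint is tied to the primary stigma measure. The error rate and correlation are "a 5% two-tailed type I error rate, and an intra-cluster correlation coefficient (ICC) of 0.01", and no other correlation is given. On size: "We targeted a total cluster size of 12, with four schools (two primary and two secondary) grouped to crossover from control to intervention", and "we estimate that the evaluation will reach 75 students per school for a total sample of" 900. The 75 is half of the 150 eligible students per school, after participation and attrition.
- **Study design.** "each school will participate across four 8-week periods", with blocks exposed for 24, 16 or 8 of the 32 weeks.
- **Outcomes.** Assessments take place "at baseline, following each crossover period (i.e., every 8 weeks", and again five months after the last block. The primary outcomes are enacted, anticipated and internalized stigma on the adolescent HIV stigma scale.
- **Survey design and measurements.** That scale is assigned to HIV-positive students. Other scales cover courtesy stigma in HIV-affected students and perceived stigma in the community.
- **Analysis of survey data.** "The multilevel structure will be defined by assessments within participants as level one, participants as level two, and schools as level three". Random effects are planned for the school and for the student nested in it.
- **Discussion.** The design is called longitudinal, and attrition is anticipated.
- **Setting and participants.** HIV prevalence in the district is 7.2% at ages 15–24.

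**The concern.** The power paragraph departs from the rest of the article in two ways.

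First, its inputs describe students who are independent apart from a constant school ICC. The design and the analysis model follow the same students from survey to survey. The published power and the detectable difference it implies therefore belong to a different dependence structure.

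Second, it counts all 75 students in each school as contributing to the primary stigma measure, while the survey section gives that measure to HIV-positive students only. At stake is whether 98% describes the primary analysis at all. Someone planning, funding or later interpreting a null result on the primary scale would rely on that number.

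**Working it through.** **Model.** Stepped wedge with fixed period effects, a constant treatment effect, a two-sided 5% test and the normal approximation. There are 12 schools crossing over in three groups of four.

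Inputs from the article: proportions 0.60 and 0.48, ICC 0.01, and 75 students per school. The pooled variance is v = 0.54 × 0.46 = 0.2484.

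Inputs not in the article (assumed):
- r, the within-student correlation between surveys beyond the school effect
- c, the school autocorrelation (the between-period school correlation divided by the within-period one)

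With m students per school, τ² = 0.01v, σ² = 0.99v/m and T surveys, set

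a = cτ² + rσ², b = (1 − c)τ² + (1 − r)σ².

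The variance of the effect is

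Var = 12·b·(b + T·a) / (64·b + K·a).

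The constants come from the crossover pattern: 24 treated school-periods, sum of squared period totals 224, sum of squared school totals 56.
- 12×24 − 224 = 64
- K = 24² + 12·T·24 − T·224 − 12×56, which is 160 for T = 4 and 224 for T = 5

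Power = Φ(0.12/SE − 1.96). The difference detectable with 90% power is 3.2415 × SE.

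**Step 1: the article's own figure.** Take T = 4, m = 75, r = 0, c = 1. Then τ² = 0.002484 and σ² = 0.003279.

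Var = 12 × 0.003279 × (0.003279 + 0.009936) / (0.20985 + 0.39744) = 0.000856, so SE = 0.0293 and power = **98.4%**. This matches the stated 98%. Dividing the 75 students over four periods (18.75 each) gives only about 60%, so the match needs 75 students in every period.

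**Step 2: number of surveys.** A baseline survey plus one after each of four 8-week periods gives five (weeks 0, 8, 16, 24, 32). All schools are in control at weeks 0 and 8. With T = 5, r = 0, c = 1: SE = 0.0284 and power 98.8%. The difference from four surveys is trivial.

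**Step 3: cohort, 75 per school.**

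| r | T=4, c=1 | T=5, c=1 | T=5, c=0.5 | Detectable difference, T=5, c=1 |
|---|---|---|---|---|
| 0 | 98.4% | 98.8% | 96.3% | 9.2 points |
| 0.3 | 99.75% | 99.86% | 98.4% | 7.8 |
| 0.5 | 99.98% | 99.99% | 99.4% | 6.7 |
| 0.7 | about 100% | about 100% | 99.9% | 5.2 |

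Each student is compared with him- or herself over time, so a positive r lowers the variance. Decay of the school correlation works the other way.

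**Step 4: the students who answer the primary scale.** Applying 7.2% to 75 gives 5.4 per school, or about 65 in 12 schools. At T = 5, c = 1, r = 0: σ² = 0.04554 and Var = 12 × 0.04554 × 0.05796 / (2.91456 + 0.55642) = 0.00913. SE = 0.0955 and power is 24%.

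| r | Power, 5.4 per school | Detectable difference | Power, 10.8 per school |
|---|---|---|---|
| 0 | 24% | 31.0 points | 41% |
| 0.3 | 28% | 28.3 | 49% |
| 0.5 | 35% | 24.5 | 61% |
| 0.7 | 52% | 19.3 | 81% |

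The last column doubles the group, as if all 150 eligible students took part (0.072 × 150 = 10.8) or prevalence were twice as high. With 5.4 per school, c = 0.5 changes little (24% at r = 0, 49% at r = 0.7).

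**The case against.** The case for leaving the paragraph alone has four parts.

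**The omitted term raises power.** With the other inputs held, leaving it out is a safe and common simplification, and the article notes that even ICC estimates are lacking in this setting. This stands. A reader might infer that the same students are counted repeatedly as new ones and that 98% is therefore inflated. The documents do not support that: in this design the omission understates precision.

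**The match to 98% does not prove the method.** A reader might infer that only a zero within-student correlation yields the figure. That is not so once the school correlation may decay: five surveys, c = 0.5 and r of 0.2 to 0.3 give 97.7% to 98.4%. The cross-sectional reading is the simplest, not the only one. This also stands.

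**The alarming figures come from the size of the group.** This is correct. Going from 75 to 5.4 students per school takes power from 98.8% to 24% before any within-student correlation enters, and the correlation then brings some of it back. It follows that the population is the main point and the correlation the lesser one.

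**The 5.4 is borrowed.** The 7.2% applies to ages 15–24, while the sample starts at age 10. The article gives no figure for the sample itself, so the small-group results are conditional. Even so, doubling the group leaves power between 41% and 81%.

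The brevity of a journal article does not answer the population point. The article publishes the number, ties it to the primary measure and states who answers that measure.

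**Conclusion.** The concern holds in a limited form. The stated 98% is arithmetically reproducible, but it describes 75 students per school with no within-student correlation. The article elsewhere describes a resurveyed cohort and a primary scale answered by HIV-positive students.

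For 75 per school, the dependence mismatch moves power to somewhere between about 96% and nearly 100%, depending on assumed correlations. It gives no reason to doubt the sample of 900.

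For the primary scale as the article defines its respondents, 98% is not supported. If 7.2% applies, power for 12 points is about 24% to 52% for within-student correlations of 0 to 0.7, and the detectable difference is about 31 to 19 points. These figures rest on the borrowed prevalence, the assumed correlations, categorical period effects, a constant treatment effect and a normal approximation that is rough with about five students per school.

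**What to change.** Restate the Power calculation with the closed-cohort stepped-wedge formula and five survey points (weeks 0 to 32). Give power and detectable difference separately for the population that answers each primary outcome, with the expected number of HIV-positive students per school and its source. Show results over within-student correlation 0 to 0.7 and school autocorrelation 0.5 to 1, with every assumed value labelled. Varying only the within-student correlation would print a more reassuring number than 98% for 75 per school and hide the element that can lower it.

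The cost is about an hour of calculation and one reworded paragraph, with no change to enrolment. The drawback is a less favourable stated power for the primary scale.
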